### Primary objective

The primary objective of this study is to show that long BPL leads to a greater percent total weight loss (%TWL, superiority), while not leading to a larger nutritional deficiency rate (non-inferiority) at 1-, 3-, and 5-year follow-up.

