### Study endpoints

#### Primary endpoint

The primary endpoints are %TWL and the number of nutritional deficiencies 1, 3, and 5 years postoperatively. For the %TWL the presurgical weight (at hospital entry time of the patient) and postsurgical weight at the corresponding visit will be measured.

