### Statistical analyses

#### Sample size

Our study was designed to evaluate whether long BPL in RYGB has advantages compared to short BPL in terms of % weight loss (superiority) without compromising the safety in terms of nutritional deficiency rate (non-inferiority) at 5 years follow-up. For our primary outcome efficacy and safety, assuming a %TWL of 27 ± 10% at 5 years follow-up for short BPL with a minimal improvement of 5% TWL for long BPL to be relevant and an expected cumulative nutritional deficiency rate of 50% at 5 years follow-up with a non-inferiority margin defined at 10%, 400 patients per group will be needed to reach a power of 80% with an alpha level at 5%. For further details on calculations, see the “Analysis of endpoints” section below.

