#### Analysis of primary endpoint

The primary objective consists of two separate analyses, one for safety and one for efficacy. The difference in efficacy is tested by performing a Mann-Whitney *U* test, thereby releasing the assumption of normality for the proportion of weight loss. The proportion of safety events during the first 5 years in each study arm is reported, including the two-sided 95% confidence interval.

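### The co-primary safety endpoint does not account for nutritional deficiencies present before surgery; if persisting ones count as events, the comparison with the 10-point margin is biased towards non-inferiority for new deficiencies

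*Protocol article*

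**What the plan says.** All references are to the protocol article.

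- **Primary objective:** long BPL should give greater weight loss "while not leading to a larger nutritional deficiency rate (non-inferiority) at 1-, 3-, and 5-year follow-up".
- **Primary endpoint:** the safety half is "the number of nutritional deficiencies 1, 3, and 5 years postoperatively". For the weight half, the same section names the presurgical reference weight. No reference state is named for deficiencies.
- **Sample size:** the plan assumes "an expected cumulative nutritional deficiency rate of 50% at 5 years follow-up", a non-inferiority margin of 10%, 400 patients per group, 80% power and a 5% alpha level.
- **Analysis of primary endpoint:** "The proportion of safety events during the first 5 years in each study arm is reported", "including the two-sided 95% confidence interval". No between-arm safety comparison is described.
- **Study visits and Table 1:** the panel includes vitamins A, B1, B6, B12 and D, ferritin, folate and zinc. Laboratory tests and primary variables are marked at screening, at visit 2 (0–5 days) and at every later visit.
- **Exclusion criteria:** deficiency at baseline is not listed.
- **Secondary endpoints:** for comorbidities there is a de novo category, reserved for conditions absent at baseline.

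**The concern.** The safety question is whether the longer limb causes more deficiency. A low value that predates surgery and is still low at the first postoperative sample says little about that, yet nothing in the endpoint wording keeps it out. The analysis window covers the first 5 years, and laboratory tests are scheduled from days 0–5.

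Randomisation makes such cases about equally common in both arms. Once a patient counts as an event because of a carried-over deficiency, a new deficiency caused by the operation cannot change that patient's status in a per-patient proportion. The observed difference therefore shrinks. In a superiority test this would cost power. In a non-inferiority test against a fixed absolute margin, it makes a favourable safety conclusion easier to reach.

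The deficiency comparison also appears to set the trial's size, because the weight-loss comparison alone needs far fewer patients.

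**Working it through.** **Inputs from the article:** cumulative deficiency rate 50%; margin 10%, read as 10 percentage points; 400 per arm; power 80%; two-sided 95% interval, equivalent to a one-sided 2.5% test; weight-loss SD 10 and difference 5.

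**Assumed inputs:** the share b of patients deficient at baseline (10% to 40%); all of them persist and count, equally in both arms.

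**1. The plan's own figure.** With 50% in both arms:

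n = (1.960 + 0.842)² × (0.5×0.5 + 0.5×0.5) / 0.10² = 392.4, so 393 per arm.

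This reproduces the stated 400. Power at 400 is Φ(0.10/√(0.5/400) − 1.960) = Φ(0.868) = 80.7%. A one-sided 5% level gives 310 and does not reproduce it. Weight loss alone needs about 2 × (2.802)² × 10²/5² ≈ 63 per arm.

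**2. Dilution.** Let r be the new-deficiency rate in the short-limb arm among patients free of deficiency at baseline, and r + 0.10 the rate in the long-limb arm, so the true excess equals the margin. The counted rates are:

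- short limb: p₀ = b + (1 − b) r
- long limb: p₁ = b + (1 − b)(r + 0.10)

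The counted difference is (1 − b) × 0.10.

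**3. Chance of declaring non-inferiority:**

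P = Φ( [0.10 − (p₁ − p₀)] / √{[p₀(1 − p₀) + p₁(1 − p₁)]/400} − 1.960 )

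There are two readings of the 50%. In reading A it includes baseline cases, so p₀ = 0.50 and r = (0.50 − b)/(1 − b). In reading B it is the rate of new deficiencies, so r = 0.50 and baseline cases come on top.

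Example, reading A, b = 20%: r = 0.375, p₁ = 0.2 + 0.8 × 0.475 = 0.58, SE = √[(0.25 + 0.2436)/400] = 0.0351, P = Φ(0.02/0.0351 − 1.960) = Φ(−1.39) = 8.2%.

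| b | Counted difference (points) | P, reading A | P, reading B |
|---|---|---|---|
| 0% | 10 | 2.5% | 2.5% |
| 10% | 9 | 4.7% | 4.7% |
| 20% | 8 | 8.2% | 8.6% |
| 30% | 7 | 13.4% | 14.8% |
| 40% | 6 | 20.5% | 24.7% |

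A simulation of reading A with 400,000 replicates gave 2.5%, 4.7%, 8.2%, 13.5% and 20.8%.

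**4. Counting only new deficiencies in baseline-free patients.** The error returns to 2.5% in every row. Power with 400(1 − b) patients per arm and no true difference is Φ(0.10/√{2r(1 − r)/[400(1 − b)]} − 1.960). For b = 10%, 20%, 30% and 40% this is 77.0%, 74.3%, 74.5% and 83.6% under reading A, and 76.5%, 71.6%, 65.8% and 59.1% under reading B.

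**The case against.** A reader might infer that the protocol counts every deficiency, pre-existing ones included. The article does not say so. It leaves the safety event undefined, and a cumulative rate can be read as the incidence of deficiencies arising after surgery. The full protocol or the analysis plan may settle this. That stands, so the point is put conditionally. It remains that the article, which draws the baseline distinction for a secondary endpoint, draws none for a co-primary one.

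A reader might also infer that the type I error of the planned test is inflated as such. That does not follow either. If the 50% and the margin refer to all deficiencies over 5 years, the test holds 2.5% for that quantity. The inflation concerns a conclusion about new deficiencies, and the article does not say which is meant.

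Other objections also stand in part:

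- The article gives no baseline share. If it is small, or if deficiencies are corrected before they can count, the effect is small.
- Randomisation balances baseline prevalence, not persistence. If a longer limb makes an existing deficiency harder to correct, persistence differs between arms and is itself a safety signal. A new-onset-only endpoint would discard it.
- The calculation applies to the per-patient proportion in the analysis section. The number of deficiencies named as the endpoint would not saturate in the same way.
- Screening data are not ruled out of the analysis, since Table 1 marks primary variables at screening. Their use is unstated.

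**Conclusion.** The point holds in conditional form. The endpoint, sample size and analysis wording neither exclude nor account for deficiencies present before surgery, although the data to do so are planned. If persisting baseline deficiencies count, the between-arm difference falls to (1 − b) of its value among baseline-free patients. A true 10-point excess in new deficiencies would then pass as non-inferior with a probability of about 5% (b = 10%) to 20–25% (b = 40%), instead of 2.5%.

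The direction is clear under these conditions; the size is not. It rests on an assumed b, on all baseline cases persisting equally in both arms, and on the margin being meant for new deficiencies. This is a gap worth closing before analysis, not proof that the trial will reach a wrong safety conclusion.

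**What to change.** 1. Replace the per-arm proportions as the primary safety analysis with a test of the between-arm risk difference. Compare the upper limit of its two-sided 95% interval with the 10-point margin, adjusting for baseline deficiency status from the screening laboratory values and for centre, the stratification factor.
2. State whether the 50% rate and the margin refer to new or to all deficiencies.
3. Report new-onset deficiencies (analyte normal at screening) alongside all deficiencies, and require consistent conclusions before claiming non-inferiority. This keeps persistence and worsening in view.

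The third step is essential, because adjustment alone does not undo the dilution. A difference averaged over baseline strata is still (1 − b) × 10 points, now with a smaller standard error. In the b = 20% example of reading A, SE = √[0.8 × (0.375×0.625 + 0.475×0.525)/400] = 0.0311, and P = Φ(0.02/0.0311 − 1.960) = 9.4%, against 8.2% unadjusted.

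**Cost:** a little more analysis work and revised wording; no new data. The expected rate and power may need restating. If only baseline-free patients are analysed and the 50% includes baseline cases, power at 400 per arm is about 74–84% for b = 10–40%, and 80% power needs about 432, 460, 459 and 365 randomised per arm for b = 10%, 20%, 30% and 40%. Defining new onset by analyte keeps in the analysis patients deficient in only some analytes, so these power figures would not carry over unchanged.

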#### Analysis of secondary endpoints

To investigate superiority of the experimental treatment in the long-term, analysis used for the primary endpoint will be repeated for %EBMIL at 1, 3, and 5 years postoperatively. The number of peri- and post-surgical complications will be analyzed by the chi-squared or Fisher’s exact test dependent on the CCI score. The other secondary endpoints will be investigated using appropriate explorative methods and graphical visualization.

### Ethical considerations

Participation in this trial is strictly voluntary and patients are allowed to exit the trial at any point without explanation. All eligible patients are provided an information brochure describing the study with sufficient information for them to make an informed decision about their participation in this study.

The study protocol, patients’ information sheets and informed consents were approved by the local ethic committee (Ethikkommission Nordwest- und Zentralschweiz, EKNZ 2019-02392). In addition, insurance coverage for general liability has been obtained.

Patients who decline to participate in this study are treated according to clinical standards. These patients will not be included and no study-specific follow-up will be performed.

### Participants’ confidentiality

The participants’ confidentiality is maintained at all times. For confidentiality reasons, electronic case report forms (eCRF) do not contain any personal data of study participants. Members of the ethics committees are obliged to respect confidentiality and to refrain from divulging the participants’ identity or any other personal information they might be aware of. Source data in the hospital’s electronic patient information systems are secured by personal passwords and handled with respect to medical secrecy.

### Archiving and data retention

The investigator will maintain all study-related records, such as eCRFs, medical records, laboratory reports, informed consent documents, safety reports, information regarding participants who discontinued, and other pertinent data. All records will be retained by the investigator as long as required by the applicable laws and regulatory requirements (10 years). Thereafter, all data will be destroyed. The study is conducted in compliance with this protocol and according to Good Clinical Practice standards as well as legal regulations. Direct access to source documents will be permitted for purposes of monitoring, audits, and inspections.

### Dissemination policy

The results of the study will be published in a peer-reviewed medical journal and presented at national and international scientific conferences. Authorships will be based on the recommendations of the International Committee of Medical Journal Editors.

## Discussion

The positive effects of bariatric surgery on weight loss, obesity-related comorbidities, and mortality have been widely demonstrated in long-term cohort trials and short-term RCTs [26, 27]. Over time, these procedures have improved in respect to safety and can be offered at a low mortality and morbidity [28]. The sleeve gastrectomy and the RYGB are the most common surgical procedures [8]. However, the laparoscopic RYGB is still the most commonly performed bariatric procedure in Switzerland [17]. It is no longer a question, if the RYGB has a significant effect on weight loss and on obesity-associated comorbidities, but rather how to improve the procedure and its outcomes.

The RYGB is a complex anatomical concept with various parts for potential improvement including the limb lengths. For many years, the length of the AL was thought to be the most influential factor regarding postoperative weight loss. Therefore, previous studies focused on the effects of various AL lengths, until Choban et al. showed that lengthening the AL has no effect on weight loss [29]. In contrast, the effect of the BPL length on weight loss has been studied to a much lesser extent. While the non-randomized study by Leifsson et al. reported excellent weight loss in patients with long BPL [14], only one RCT addressed this question after RYGB so far [16]. Here, the authors compared long BPL RYGB (150 cm BPL, AL 75 cm) with a short BPL RYGB (BPL 75 cm, AL 150 cm) in 128 patients and found a significant increase in %EWL for patients with long BPL RYGB 4 years after surgery. However, lengthening the BPL is not unlimited due to the increased risk of malnutrition [30]. Several studies suggest a minimal total alimentary limb length of 300 cm, which is defined as an added value of the AL and the CL, to reduce the risk of malnutrition with deficiencies of micro- and macronutrients [31–33].

Against this theoretical framework, it is difficult to draw conclusions on the optimal length of the AL and BPL, respectively, necessary to achieve the best possible outcome with a low risk of protein malnutrition. The most effective BPL length for the RYGB procedure has not been found yet since weight loss and improvement of comorbidities have only been evaluated in one non-randomized study [14] and one RCT [16].

As total bowel length varies by many meters between individuals, measuring the total length and therefore knowing the dimensions of all segments involved in RYGB will lead to a better understanding of the role of each segment in the beneficial effects after RYGB. This study investigates the effectiveness of long BPL RYGB compared to short BPL RYGB, analyzing defined clinical endpoints such as weight loss, morbidity and mortality, improvement in obesity-related comorbidities, and quality of life. Furthermore, the RCT by Homan et al. [16] failed to show any significant differences in T2DM remissions as it was only powered for weight loss. Our study has enough power to address the postoperative course in terms of resolution of comorbidities.

In conclusion, the “perfect” RYGB leads to adequate %TWL and improvement in obesity-related comorbidities without increasing the complication rate. The SLIM trial will answer questions about effectiveness and safety after long BPL RYGB and provide level I evidence for improvement of the standard RYGB. These findings might therefore potentially influence bariatric surgery guidelines on a global level.

## Trial status

Protocol version number 1.1, 12 February 2020. The trial has received ethics approval by January 2020. The first patient will be randomized in June 2020. We expect to enroll the calculated sample size in a 2- to 3-year time period. Estimated end of the study is December 2027.

## Data Availability

All data will be available for other research groups interested in conduction systematic reviews. Requests for data should be directed to the Sponsor Investigator, [name], [contact].

## Abbreviations

AL: Alimentary limb
BAROS: Bariatric analysis and reporting system
BMI: Body mass index
BPD: Biliopancreatic diversion
BPL: Biliopancreatic limb
CCI: Comprehensive Complication Index
CDC: Clavien-Dindo classification
CL: Common limb
EBMIL: Excess body mass index loss
eCRF: Electronic case report form
EWL: Excess weight loss
GIQLI: Gastrointestinal quality of life index
RYGB: Roux-en-Y gastric bypass
TALL: Total alimentary limb length
TWL: Total weight loss
